### Sample size

A power analysis was conducted using the two primary outcome measures—the Strengths and Difficulties Questionnaire (SDQ) and the Systematic Clinical Outcome and Routine Evaluation (SCORE-15)—in order to identify the minimum sample size required to detect an improvement in child and family psychosocial functioning post intervention.

Three of the previous RCTs of FT employed intensive clinician interviews to assess child psychosocial functioning and reported statistically significant results with varying sample sizes (*n* = 28–105) [23–25]. Similar to two previous evaluations of FT [26, 27], this study intends to use the brief SDQ to measure child psychosocial functioning. These studies reported effect sizes of 0.70 and 1, respectively, at post intervention. The Finnish study [26] involved 109 families and the German study [27] recruited 37 families. The power calculation for the current study was conducted for an independent samples *t*-test, as this is expected to be the least powerful test in the overall main analysis. Using G*Power *t*-test calculations for the difference between two independent means (two groups), and assuming *α* = .05, 80% power, two tailed testing, 15% attrition, and 2:1 allocation, the study will need to recruit 38 participants (FT = 25, TAU = 13) to detect a change between 0.7 and 1. Given that the effect sizes in these two studies are large, we intend to recruit additional families to enable us to detect smaller changes, where they exist.

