Family functioning has not been typically assessed in previous evaluations of FT despite the fact that enhanced family communication and cohesion are key intervention goals. One previous study has assessed family functioning using intensive clinician interviewing of families [25], although it should be noted that two ongoing evaluations of FT have included it as an outcome, albeit using measures that take considerably longer to administer than the SCORE-15 [28, 29]. The SCORE-15 has been used as a brief measure of family functioning in evaluations of family therapy with populations that share a clinical profile similar to the sample in the current study [53]. An effect size of 0.5 was reported. Similar to above, we conducted a G*Power *t*-test calculation for the difference between two independent means (two groups) for the outcome of family functioning. Assuming *α* = .05, 80% power, two tailed testing, 15% attrition, and 2:1 allocation, the study will need to recruit 144 participants (FT = 96, TAU = 48) to detect a change of 0.5.

These sample sizes should be more than sufficient for mixed model repeated measures (MMRM) across the three time points to have > 80% power and also allow for post hoc *t*-tests both between groups and within groups to have ≥ 80% power.

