#### Statistical methods

Data presentation and results will be carried out according to Consolidated Standards of Reporting Trials (CONSORT) guidelines for RCTs. Descriptive statistics (means, standard deviations, frequencies) will be used to describe the pre-treatment characteristics of participants and for primary and secondary outcome measures at each time point. Mixed model repeated measures (MMRM) will be used to investigate the effects of the intervention at two between (intervention and control) and three within (pre-intervention, 6- and 12-month follow-ups) levels for all primary and secondary outcome measures (all continuous outcome data). Initial MMRM analysis will control for baseline psychopathology as a fixed covariate. Modelling for the primary outcomes will be conducted using an unstructured repeated measures covariance matrix and all other variables as fixed effects. Mean difference effect sizes, 95% CIs, and *p* values will be reported for continuous outcomes. Where parametric test assumptions fail significantly, then non-parametric tests will be used.

MMRM was chosen as the primary method for analysis as it can reduce several analytic problems that may arise within the current study. Firstly, it allows for different numbers of measurements per participant, thereby tolerating a level of missing data, which is particularly problematic with RCTs with vulnerable populations, as follow-up data are often collected many months after treatment has ended and participants may be difficult to contact [59]. This enables us to use all of the data collected as opposed to deleting cases or imputing missing values. Secondly, it has the advantage of modelling change within individuals as well as across groups. Singer and Willet [60] identify this as the best approach for longitudinal data that has three or more time points.

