The analysis will follow an intention-to-treat (ITT) principle where all randomised participants, including those who stop receiving the intervention, will be analysed ‘as randomised’. MMRM analysis is a maximum likelihood statistical modelling technique whereby mean estimates and the repeated measures covariance structure for the observed data are based on a statistical model and possible values are generated for the missing data [61]. Attrition will also be analysed to assess the differences between those who ‘dropped out’ and those who stayed, and to assess if there are predictors at baseline to indicate differences. Qualitative data will also inform the identification of predictor variables for attrition. MMRM will be the primary analytic method, although *t*-tests will be used to provide detail on any significant differences found from the MMRM.

Regression techniques will be used to explore whether intervention effects differ for certain participant groups such as age of children, severity of parental mental illness, other parent also has a mental illness, and socioeconomic status. Analysis will be conducted using SPSS software (IBM SPSS Statistics version 26).

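### The non-parametric fallback and the post hoc t-tests give up the adjustment and missing-data handling for which MMRM was chosen; follow-up contrasts should come from the fitted model, with within-group changes descriptive only

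*Protocol article*

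**What the plan says.** Under Statistical methods, MMRM is the analysis for all primary and secondary outcomes, with baseline psychopathology as a covariate, and mean differences are to be reported with 95% CIs and p values. The stated reason for choosing MMRM is that it uses every observation collected, without deleting cases or imputing. The Outcomes section likewise commits all impact measures to covariance-adjusted analysis.

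Two further provisions sit beside this:

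- A fallback, in Statistical methods: "Where parametric test assumptions fail significantly, then non-parametric tests will be used". No criterion and no test is named.
- Follow-up tests. Statistical methods confirms MMRM as primary and says that t-tests "will be used to provide detail on any significant differences found from the MMRM". Sample size shows which t-tests are meant: the planned numbers are said to allow post hoc t-tests "both between groups and within groups to have" at least 80% power.

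Under Participant timeline, only the Family Talk arm is assessed at 12 months, so any t-test of change to that point is necessarily within-group.

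**The concern.** The fallback allows a different method to replace the primary model, depending on the data. A standard two-sample rank test is unadjusted, uses complete cases and gives no adjusted mean difference. It therefore departs from three commitments made elsewhere in the same article.

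The between-group t-test departs from the first two in the same way. It has less power than the model it is meant to explain, so it can contradict that model.

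Within-group tests answer a different question: whether an arm changed, not whether the arms differ. With 96 families in one arm and 48 in the other, the same change reaches significance more easily in Family Talk. At stake is a report that says Family Talk improved and controls did not, when both changed equally.

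**Working it through.** **Inputs from the protocol article (Sample size).** Two-sided alpha .05; "80% power, two tailed testing, 15% attrition, and 2:1 allocation, the study will need to recruit 144 participants", split 96 and 48; for SCORE-15, "An effect size of 0.5 was reported". The calculation is for an independent-samples t-test, "as this is expected to be the least powerful test in the overall main analysis".

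**Assumed, because the article gives none.** Correlation r between baseline and 6-month scores of 0.5 to 0.7; a common improvement of 0.2 to 0.4 SD in the null scenarios; one score per family; a baseline-adjusted comparison (ANCOVA) at 6 months standing in for the MMRM group contrast.

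**1. The plan's own figure.** Noncentrality = d × √(n1·n2/(n1+n2)).
- 96 and 48: 0.5 × √32 = 2.83, power 80.2%. So 144 is reproduced for the t-test with every family retained.
- After 15% loss, 96 × 0.85 ≈ 82 and 48 × 0.85 ≈ 41: 0.5 × √(82 × 41/123) = 2.61, power 73.7%. Whether 144 should have been inflated for attrition is a separate matter; 82 and 41 serve here as the analysed sample.

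**2. Adjusted contrast, same families.** Adjustment multiplies the residual SD by √(1 − r²), so the effective d is 0.5/√(1 − r²).

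| r | effective d | power, 82 and 41 | SE of unadjusted relative to adjusted |
|---|---|---|---|
| 0.5 | 0.577 | 85% | 1.15 |
| 0.6 | 0.625 | 90% | 1.25 |
| 0.7 | 0.700 | 95% | 1.40 |

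In simulation at d = 0.5 and r = 0.5, the unadjusted t-test was non-significant in about 16% of the trials in which the adjusted contrast was significant. A t-test on change scores would not help at r = 0.5, since the SD of change is √(2(1 − r)) = 1; at higher r it would recover part of the loss.

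**3. The fallback, if it means a Shapiro test followed by Mann-Whitney.** With skewed scores (gamma, shape 4), r = 0.6, d = 0.5 and 82 and 41 families, two set-ups gave power falling from 0.883 to 0.826 and from 0.895 to 0.768, with the switch triggered in 82% and 98% of runs. Type I error stayed at about 0.045 in the second set-up. The loss is therefore about 6 to 13 points, sensitive to the assumed data, with no inflation of false positives.

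**4. Within-group tests with no treatment effect.** Both arms improve 0.3 SD, r = 0.5, so the standardised change is 0.3/√(2 × 0.5) = 0.3. Noncentrality = 0.3 × √n.
- Family Talk, n = 82: 2.72, significant in 76.6%.
- Control, n = 41: 1.92, significant in 46.6%.
- Family Talk only: 0.766 × (1 − 0.466) = 0.409. Control only: 0.466 × (1 − 0.766) = 0.109.
- At 1:1 (61 and 61) each test is significant in 63.5%, and each one-sided pattern occurs in 0.635 × 0.365 = 23%. The tilt comes from the 2:1 ratio.
- Over improvements of 0.2 to 0.4 SD and r = 0.5 to 0.7, the Family-Talk-only pattern ranges from 10% to 41% and always exceeds control-only.

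**5. Effect of running t-tests only after a significant MMRM result** (scenario of step 4, simulated):

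| what must be significant first | Family-Talk-only pattern in null trials |
|---|---|
| nothing | 41% |
| a time effect alone (change pooled over all families) | about 40% |
| the adjusted group difference | about 2% to 3% |

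**The case against.** The strongest reply is that MMRM stays primary and the t-tests come only after it has found something. A reader might take 41% as the trial's false-positive rate; the article does not support that. If the significant finding must be a group difference, the misleading pattern occurs in 2% to 3% of null trials, inside the primary test's own 5%. This stands. What remains is that the article speaks of any significant difference from the MMRM and does not confine it to the group contrast. A time effect, which is likely if both arms improve, would then be enough, and the rate returns to about 40%.

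A reader might also infer that within-group p values will be compared across arms. The article never says so: within-group tests appear only in a remark about power, and at 12 months within-arm change is all that can be described for Family Talk. The harm depends on how the tests are read.

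Nor does the wording establish that a formal significance test decides the switch, or that the replacement is an unadjusted rank test. The trigger may simply mean a substantial failure of assumptions, and an adjusted rank method is not excluded. Such details may stand in an analysis plan not shown, so their absence is not the point here. The point is that the article states a replacement where it could have kept the adjusted model, and that the standard tests of that name break its other commitments.

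**Conclusion.** The point holds as a weakness in the analysis wording. It does not show that the primary test is invalid, and nothing here indicates inflated type I error. The follow-up t-test has 74% power where the adjusted contrast has 85% to 95%, and at r = 0.5 it contradicts a significant adjusted result about one time in six. Within-group tests do not estimate the randomised effect, and 2:1 allocation tilts them towards Family Talk (77% against 47% significant for the same 0.3 SD change). How often that could mislead runs from 2% to 3% up to about 40% of null trials, depending on which MMRM result is allowed to trigger the t-tests, which the article leaves open. The figures rest on 15% attrition, d = 0.5, one score per family, and the assumed correlations and improvements. The direction does not depend on the particular values chosen within those ranges.

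**What to change.** 1. Keep the adjusted model as primary for every outcome. If residuals are skewed, report the same contrast with robust standard errors or a bootstrap that resamples families, since up to two children per family take part (Recruitment). Any rank analysis is a sensitivity analysis only.
2. Replace the post hoc between-group t-tests with the adjusted 6-month group difference and its 95% CI from the fitted model.
3. Label within-group changes, including the 12-month change in the Family Talk arm, as descriptive and not as evidence of a treatment effect. Amend the power remark in Sample size to match.

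The cost is a few sentences in the analysis text and a few lines of code. No new data and no change for families are needed.

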#### Process evaluation analysis

The qualitative data (interviews, focus groups, meeting minutes) will be coded and organised using MAXQDA and analysed using constructivist grounded theory [62]. The analysis will be informed by the MRC framework for process evaluations and located within an implementation science framework [35, 48]. One researcher will code all the data, with inter-reliability of codes checked by another researcher on 25% of transcripts selected at random. Any differences encountered by the researchers will be discussed and resolved between them.

We will use descriptive statistics to analyse measures of fidelity (therapist adherence, family attendance), and the Family Satisfaction Questionnaire. Frequencies, medians, interquartile ranges, means, and standard deviations will be reported as appropriate.

#### Economic evaluation

The economic evaluation will compare the cost-effectiveness of receiving FT versus a services as usual control group on our primary outcomes at 6-month follow-up. The cost-effectiveness analysis CEA will be undertaken in three key steps:
(i)Identify the cost of delivering FT, obtained through cost diaries completed by service providers(ii)Compare service utilisation for the intervention and control groups conditions (completed by parents on the Services Utilisation Questionnaire at baseline and 6-month follow-up); and(iii)Calculate an incremental cost-effectiveness ratio (ICER) to give the cost of obtaining a one unit decrease on the clinical outcome measures employed in the RCT (i.e. SDQ, SCORE-15) when comparing FT to usual services at 6-month follow-up.

The ICER will use a 1000 replication bootstrap to provide a 95% confidence interval accompanied by appropriate sensitivity analyses (e.g. excluding non-recurrent costs of training). The ICER accommodates sampling (or stochastic) uncertainty and varying levels of willingness to pay for reductions in the primary outcomes of interest. The CEA will adopt a multiagency, public sector, analytic perspective and will use official sources (e.g. government pay scales, the Casemix/HIPE unit of the Health Service Executive) to provide estimates of unit costs separate from frequencies of resource utilisation.

#### Monitoring

A data monitoring committee is not feasible for this trial due to its relatively short duration and size. Only the research team will have access to the data. The data-input manager will ensure that the quality of data is maintained throughout the trial. Only the data-input manager and the team statistician will have access to the outcome data and they will be blind to study groups. The fieldwork coordinator will inform the research team of any issues arising with participant recruitment and data collection.

Due to the relatively short duration of this trial, we will not conduct an interim analysis as sufficient data will not be available at that point. The trial will only be stopped by the principal investigator (in conjunction with the PRIMERA funders) if it becomes clear that harm is being caused by the intervention or recruitment rates are unacceptably low.

The research team will report quarterly to the study’s Steering Group on trial conduct and progress. The Steering Group comprises high-level management from the HSE and Tusla, service users, and representatives from mental health advocacy groups and the academic sector.

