**Methods:**

The study comprises a multi-centre, randomised controlled trial (RCT), with nested economic and process evaluations, to assess the clinical and cost-effectiveness and implementation mechanisms of Family Talk compared to usual services. The study is being conducted in 15 adult and child mental health settings in Ireland. Families with a parent with mental illness, and children aged 5–18 years (*n* = 144 families) will be randomised to either the 7-session Family Talk programme (*n* = 96) or to standard care (*n* = 48) using a 2:1 allocation ratio. The primary outcomes are child psychosocial functioning and family functioning. Secondary outcomes are as follows: understanding and experience of parental mental illness, parental mental health, child and parental resilience, partner wellbeing and service utilisation. Blind assessments will take place at pre-intervention and at 6- and 12-month follow-up.

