### Trial design

The current study is designed as a multi-centre, randomised, controlled, investigator-blinded superiority trial with two parallel groups and a primary endpoint of child psychosocial functioning and family functioning at 6-month follow-up. Randomisation will be performed as block randomisation with a 2:1 allocation (intervention: control).

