### Participant timeline

The flow of participants from recruitment through to the end of the study is shown in Fig. 2. Parents and children will be assessed at T0 (pre-intervention), at 6-month follow-up (T1; 3 months post intervention), and at 12-month follow-up (T2). Assessment of the control group will continue up to T1, after which they will be offered FT. Assessment of the intervention group alone will continue at 12-month follow-up. Enrolment into the study will be on a staggered basis and will depend on clinicians referring suitable families to the research team.

Data collection and delivery of the intervention were necessarily paused for 4 months (mid-March to mid-July 2020) due to the COVID-19 lockdown restrictions in the RoI. Therefore, assessments affected by the restrictions will be collected 4 months later than originally planned. However, taking the pause into account, we still consider the assessment time points to be 6- and 12-month follow-up. Assessments affected by the COVID-19 suspension will be noted in the analysis.

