### Blinding

Due to the nature of the intervention, neither participants nor practitioners can be blinded to allocation. Outcome assessors will be blinded to treatment allocation, as well as those conducting the statistical analyses. Randomisation will be conducted by an external consultant who is unconnected to the recruitment, data collection, or analysis process. Participants (families), and practitioners will be requested not to disclose their group allocation to the research team. Any evidence of unblinding will be taken into account at the analysis stage.

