### Data collection

#### Families

Participants will be invited to complete outcome measures at baseline (T0) and at 6- and 12-month follow-up periods (T1 and T2) (Fig. 2). Each questionnaire will be coded with the participant’s ID number, date of completion, version (baseline, T1, T2), and the researcher’s name. Qualitative data (i.e. interviews) will be collected from families following the 6-month assessment within the RCT. Copies of the impact evaluation and costs measures, and interview schedules for the process evaluation, can be obtained from the PRIMERA programme coordinator (https://cmhcr.eu/primera-programme/).

For all aspects of the evaluation (RCT, costs and process evaluations), data will be collected by a researcher who will meet with the participant in the family home, or, if preferred, in a local family/health care centre. Data will also be collected from parents by video call where it is not safe, due to COVID-19, to meet in person. Parents and children (8–18 years) will provide written informed consent/assent prior to data collection and will be assured of ethical protections (e.g. confidentiality) and risks and benefits from participation. Parents will complete a paper version of outcome measures and the assessment will take 45–75 min (with a break if required). Whilst electronic devices may sometimes improve data accuracy and the timeliness of data collection and management [55], the experience of the research team and site staff is that vulnerable populations may be alienated by their use and are more comfortable with paper-based data collection methods. Based on feedback from the mental health service professionals with whom we are working, children will be offered an option of completing a paper version of the survey in the presence of the researcher or via the secure online Qualtrics software package [56]. Both options will take 10–15 min. The online survey will include voice-recorded files in order to assist comprehension. The online survey will be accessed via the project webpage in compliance with *General Data Protection Regulation*s (GDPR). No personal identifiers of children will be collected using Qualtrics and Qualtrics does not share data with third parties [56].

For the qualitative interviews, parents and children will provide consent/assent for their interview to be digitally recorded. Anonymity and other ethical protections will be assured (Information sheets and consent/assent forms are available upon request).

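### Only Family Talk families are assessed at 12 months, so a T2 visit or record reveals the arm; the 12-month blinding claim is false and the open-ended claims need a time limit

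*Protocol article*

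**What the plan says.** The protocol article makes three blinding statements. The abstract (Methods) says: "Blind assessments will take place at pre-intervention and at 6- and 12-month follow-up". The Blinding section says: "Outcome assessors will be blinded to treatment allocation, as well as those conducting the statistical analyses". The Monitoring section says: "Only the data-input manager and the team statistician will have access to the outcome data and they will be blind to study groups". The last two carry no time limit.

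The Participant timeline section sets out who is seen when. For controls: "Assessment of the control group will continue up to T1, after which they will be offered FT". For the other arm: "Assessment of the intervention group alone will continue at 12-month follow-up".

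Two further sections bear on how far this travels. Under Data collection (Families): "Each questionnaire will be coded with the participant’s ID number, date of completion, version (baseline, T1, T2), and the researcher’s name". Under Statistical methods, the mixed model is to be fitted at "two between (intervention and control) and three within (pre-intervention, 6- and 12-month follow-ups) levels for all primary and secondary outcome measures". The Trial design section places the primary endpoint earlier: "a primary endpoint of child psychosocial functioning and family functioning at 6-month follow-up".

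**The concern.** Blinding at a visit requires that both arms could be having that visit. At T2 only one arm does. A fieldworker sent to a 12-month visit knows that the family was allocated to Family Talk. Anyone who handles a questionnaire marked T2 learns the same about that participant ID, and the ID links back to the family's T0 and T1 data.

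Two things are at stake. First, the 12-month results would be reported as blind assessments when they cannot be. Second, the protocol relies on a blind statistician while leaving some judgements open: when test assumptions have failed badly enough to change method, how suspected unblinding is allowed for, and how visits delayed by the COVID-19 pause are treated. If the statistician makes these choices on a file that already holds T2 records, the stated safeguard is largely absent for the 6-month primary comparison as well.

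**Working it through.** The contradiction needs no arithmetic. The sections line up as follows.

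1. Participant timeline: the control group has no T2 assessment, so P(Family Talk | T2 visit or record) = 100% by design.
2. Abstract: assessment at 12 months is blind. This cannot be true together with step 1.
3. Blinding and Monitoring: assessors, analysts, data-input manager and statistician are blind, without limit of time. This cannot remain true for anyone who sees a T2 visit or record.
4. Data collection: ID and version are on every questionnaire, so the arm can be read from the record itself. Coding the arms A and B does not help, because only one code can have T2 data.
5. Trial design: the primary endpoint is at T1, and each family's T1 visit comes before its T2 visit. The T1 assessor therefore learns nothing by this route.
6. Statistical methods: one model spans T0, T1 and T2. If it is fitted on a merged file, the statistician can read arm from T2 status.

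The arithmetic shows how much T2 status would reveal in a merged file. The protocol gives no figure for this, so there is none to reproduce. Inputs: 96 Family Talk and 48 control families (Sample size). T2 loss is an assumption: 15%, borrowed from the attrition rate in Sample size, and 30% as a less favourable case.

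- Family Talk families identified with certainty = 96 × (1 − loss)
- P(control | no T2 record) = 48 / (48 + 96 × loss)
- Families classified correctly by T2 status = (48 + 96 × (1 − loss)) / 144

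| T2 loss | Identified with certainty | P(control given no T2) | Classified correctly |
|---|---|---|---|
| 0% | 96 | 48/48 = 100% | 144/144 = 100% |
| 15% | 81.6, about 82 | 48/62.4 = 77% | 129.6/144 = 90% |
| 30% | 67.2, about 67 | 48/76.8 = 62.5% | 115.2/144 = 80% |

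For comparison, calling every family Family Talk is right for 96/144 = 67% under 2:1 allocation.

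**The case against.** The strongest reply is that the primary endpoint is safe. It is measured at T1, each family's T1 visit precedes its T2 visit, and a T2 record from an early family says nothing about the arm of a later one. For assessment at T1 this is right. A reader might infer that the 6-month assessments are unblinded by the design; the documents do not support that.

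A second reply is that assessor blinding protects little here. Both primary outcomes are questionnaires answered by parents and children who know their allocation, and with no controls at T2 there is no concurrent contrast for an assessor to distort. This also stands. It limits the harm at T2 but does not make the claim of blind assessment true.

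A third reply is that the order of data locks and code release is commonly left to an analysis plan, which is not shown. A reader might infer that the statistician's blinding for the 6-month analysis is lost. The protocol does not say so. Statistical methods describes a single three-time-point model, and Dissemination anticipates one paper on 6- and 12-month outcomes. These suggest a merged file, but they fix no sequence. The loss is therefore conditional.

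Finally, a reader might call allocation almost fully recoverable. At 15% loss, 23% of families without a T2 record are Family Talk families, and the overall gain is from 67% to 90%. The 15% is a sample-size assumption rather than a 12-month retention estimate, and the protocol expects the pandemic to reduce recruitment and possibly retention, so these counts are illustrative.

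**Conclusion.** The point holds in a bounded form. The claim of blind assessment at 12 months contradicts the design and is false. The unlimited claims for assessors, data-input manager and statistician cannot hold once T2 visits take place and T2 records exist. These conclusions rest on the text alone, and no analysis plan could reconcile them while T2 is confined to one arm.

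The consequence for the 6-month primary analysis depends on one assumption: that T2 data are in the statistician's file when that analysis is settled. If they are, every family with a T2 record is identified: about 82 of 96 at 15% loss, with about 90% of all families classified correctly (about 80% at 30% loss). If T2 is held back, the statistician learns nothing from it. Assessor blinding at T1 is untouched in either case.

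**What to change.** Wording:
- In the abstract, remove the 12-month time point from the claim of blind assessment.
- In Blinding and in Monitoring, limit the claims to T0 and T1. State that the data-input manager is not blind for families whose T2 records have been entered. A separate file kept from the statistician does nothing for that role.
- Describe T2 as an unblinded follow-up of the intervention arm.

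Procedure:
- Withhold T2 data from the statistician. Lock T0 and T1, fix the analysis choices, and run the 6-month primary analysis before T2 is merged.
- Withhold allocation from the statistician until the T0/T1 lock is in place and the analysis choices are fixed. Neutral codes alone are not enough, because a 2:1 split shows which group is which by size.
- Do not withhold allocation from the staff who schedule T2 visits. They need it well before the last T1 visit, since only one arm is to be seen.

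The cost is an edit to three sections, a separate T2 file and one additional data lock. T2 is analysed after T1, and the blinding as described becomes slightly less favourable. No 12-month comparison between arms is given up, because no control data are planned at T2.
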